### Procedure

At T0 (see Fig. 1), baseline assessments of daily life gait performance, gait capacity, and quality of life will be conducted. Subsequently, participants will be randomized to the intervention group (receiving the Myosuit program) or control group (initially receiving the conventional program).

**Fig. 1 Fig1:**
[figure not shown]
Schematic overview of the study design

Participants in the intervention group receive the Myosuit program which consists of five gait training sessions (in 3 weeks) with the Myosuit at the Sint Maartenskliniek. Thereafter, questionnaires regarding the usability will be delivered (T1). In addition, participants will perform a test to receive a certificate for using the Myosuit themselves at home. A 6-week home period follows, during which participants have access to the Myosuit. Measurements of daily life gait performance will be conducted during the first, third, and sixth week of the home period (T2, T3, T4). After the 6-week home period, measurements of gait capacity, usability, and quality of life will be taken at the Sint Maartenskliniek (T5).

Participants in the control group will receive four gait training sessions (in 2 weeks) at the Sint Maartenskliniek, followed by a 6-week home. Measurements of daily life gait performance will be conducted during the first, third, and sixth week of the home period (T2, T3, T4). After the 6-week home period, measurements of gait capacity and quality of life will be taken at the Sint Maartenskliniek (T5). Thereafter, the control group will as yet be enrolled in the Myosuit program which will be identical to the Myosuit program of the intervention group. Usability questionnaires will be delivered at T6 and daily life gait performance will be assessed during the first, third, and sixth week of the home period (T7, T8, T9). Measurements of gait capacity, usability, and quality of life will be taken at T10.

### Interventions

#### Myosuit program

Participants in the intervention group receive the Myosuit (MyoSwiss AG, Zurich, Switzerland) for use as an assistive device at home and in the community for 6 weeks. The Myosuit is a soft exosuit that provides antigravity support to the user’s knee and hip joints while standing and walking [16]. This light-weight wearable device (5.5 kg) supports the self-initiated movements while walking without taking over the motor control of the lower limbs [18]. Before the home period, participants receive a flyer with general exercise recommendations tailored to people with SCI. Throughout the home period, participants fill out a logbook every day recording whether and for which activities they use the Myosuit.

Before using the Myosuit at home, participants receive five individual gait training sessions at the Sint Maartenskliniek. These sessions are led by physical therapists who are experienced in treating people with SCI and who have successfully completed a Myosuit certification course. Each training session consists of two parts. During the first part (30 min per session), participants receive instructions on how to use the Myosuit independently at home. During the second part (30 or 60 min per session), participants perform functional exercises with the Myosuit, based on the FIT-Stroke exercises [28], including sit-to-stand and stand-to-sit movements, sideways movements with and without transferring objects across a distance of 3 m, balance exercises including reaching movements, stepping up and down, walking at comfortable and maximum speed, ascending and descending stairs, completing an obstacle course, and walking outside. The total training time of the second training session parts is 4 h. As for the gait training sessions, physical therapists are instructed to relate the exercises to the daily activities that participants are able to perform with the Myosuit in their home and in the community.

#### Conventional program

Participants assigned to the control group will receive four individual gait training sessions at the Sint Maartenskliniek, in which they perform the same functional exercises as the intervention group (60 min per session). The total training time is 4 h. The physical therapists are instructed to relate the exercises performed during the training sessions to the daily activities of the participants. After the training sessions, a 6-week home period follows. Similar to the intervention group, participants receive a flyer with exercise recommendations tailored to people with SCI and they will keep a logbook recording their weekly physical activities.

### Assessments

All assessments will be performed following standard procedures and conducted by the primary researcher (LV) who has been trained to perform all assessments. During all assessments, participants are allowed to use assistive devices such as walking aids and/or orthoses. If participants use an assistive device during any test, this will be documented and kept constant throughout subsequent assessments. Table 1 shows the assessments at different timepoints.

**Table 1 Tab1:** Standard protocol items: SPIRIT figure (summary of participant timeline)

	**Enrolment**	**Allocation**	**Post allocation**				**Close out RCT**	**Post allocation***				**Close out***
**Timepoint**	-T_1_	T0	T1**	T2	T3	T4	T5	T6*	T7*	T8*	T9*	T10*
**Enrolment**												
Eligibility screen	**x**											
Informed consent	**x**											
Allocation		**x**										
**Assessments**												
*Primary outcome measures*												
Walking time per day		**x**		**x**	**x**	**x**			**x**	**x**	**x**	
*Secondary outcome measures*												
Gait quality		**x**		**x**		**x**			**x**		**x**	
PWS		**x**					**x**					**x**
MWS		**x**					**x**					**x**
6MWT		**x**					**x**					**x**
SCI-FAP		**x**					**x**					**x**
SUS			**x**				**x****	**x**				**x**
D-QUEST			**x**				**x****	**x**				**x**
EQ-5D-5L		**x**					**x**					**x**
GDSSeS		**x**					**x**					**x**
*Other outcome measures*												
Demographics		**x**										

*Abbreviations*: *PWS *preferred walking speed, *MWS *maximum walking speed, *6MWT *6-Minute Walk Test, *SCI-FAP *Spinal Cord Injury Functional Ambulation Profile, *SUS *System Usability Scale, *D-QUEST *Dutch version of the Quebec User Evaluation of Satisfaction with assistive Technology, *EQ-5D-5L *European Quality of Life Five Dimension; *GDSSeS *General and Disease Specific Self-efficacy Scale, *-T*_*1 *_enrolment, *T0 *baseline, *T1 *questionnaires for the intervention group only, *T2 *first week of the home period, *T3 *third week of the home period, *T4 *sixth week of the home period, *T5 *after the intervention, *T6 *questionnaires for the control group only, *T7 *first week of the home period for the control group only, *T8 *third week of the home period for the control group only, *T9 *sixth week of the home period for the control group only, *T10 *after the intervention for the control group only

^*^Only applicable for the control group

^**^Only applicable for the intervention group

#### Primary outcome

The primary outcome measure for daily life gait performance is average walking time per day (min). It will be assessed with the Activ8 sensor (Activ8 Basic Activity Tracker, Activ8, Valkenswaard, The Netherlands), a single-unit activity monitor based on triaxial accelerometry [29]. The Activ8 will be placed on the participants’ right upper leg and measures lying, sitting, standing, walking, running, and cycling activities. Data sampling frequency is 50 Hz. The output provides information on the duration of specific activities within 1 min. The Activ8 has been validated in healthy individuals [29] and post-stroke patients [30] to assess the above-mentioned activities during daily life. Participants will wear the Activ8 continuously for seven consecutive days, 24 h a day. Baseline data (T0) will be averaged over a 7-day period to calculate the mean total walking time per day. During the 6-week home period, data from T2, T3, and T4 (the first, third, and sixth week of the home period) and data from T7, T8, and T9 (the first, third, and sixth week of the home period) will be averaged across all days (T2–T4; T7–T9) to calculate mean total walking time per day. For the primary analysis, the between-group difference in change of mean walking time per day at T2–T4 versus T0 will be of main interest.

#### Secondary outcomes

##### Spatiotemporal gait characteristics

Secondary outcome measures of daily life gait performance are walking speed (m/s), step length (m), maximum gait bout length (steps), and double support phase duration (s) assessed with inertial measurement units (IMUs). Two IMUs will be attached to both feet, and one will be positioned at the sacrum for 3 days. A self-developed algorithm comparable to previously published algorithms [31–33] will be used to calculate the various gait parameters. Spatiotemporal gait characteristics will be averaged over a 3-day period to calculate the mean at T0 (baseline). Data from the 6-week home period at T2 and T4 (first and sixth week of the home period) and at T7 and T9 (first and sixth week of the home period) will be averaged across all days (T2 + T4; T7 + T9). The between-group difference in change of spatiotemporal gait characteristics at T2 + T4 versus T0 will be analyzed.

##### Preferred walking speed (PWS)

PWS (m/s) will be assessed with the 10-Meter Walk Test (10MWT) using a static start [34]. Participants will be instructed to walk comfortably across the 10-m distance, and the time taken will be measured with a stopwatch. Participants will perform the test three times (if feasible based on their gait capacity), and the average score will be calculated. PWS will be measured at T0 (baseline), T5, and T10 (after the intervention). The between-group difference in change of mean PWS at T5 (after the intervention) versus T0 (baseline) will be analyzed. The 10MWT is a valid and reliable measure for assessing gait capacity in people with iSCI [35].

##### Maximum walking speed (MWS)

MWS (m/s) will be assessed using the 10MWT with a static start [34]. Participants will be instructed to walk across the 10-m distance as fast as possible while maintaining safety. Time required to walk 10 m will be measured with a stopwatch. Participants perform the test three times (if feasible based on their gait capacity), and the average score will be calculated. MWS will be measured at T0 (baseline), T5, and T10 (after the intervention). The between-group difference in change of mean MWS at T5 (after the intervention) versus T0 (baseline) will be analyzed.

##### Walking distance (6MWT)

Participants will be instructed to walk as far as possible during a 6-min Walk Test (6MWT) [36]. They are allowed to rest if needed, but encouraged to continue walking when possible. Participants walk in a rectangle of 4 by 18 m. Perceived exertion will be assessed before and after the 6MWT using the BORG scale (scores ranging from 6 to 20) [37]. The outcome measure of the 6MWT is walking distance (m). Walking distance will be measured at T0 (baseline), T5, and T10 (after the intervention). The between-group difference in change of walking distance at T5 (after the intervention) versus T0 (baseline) will be analyzed. The 6MWT is a valid and reliable measure to assess gait capacity in people with iSCI [35].

##### Spinal cord injury functional ambulation profile (SCI-FAP)

The SCI-FAP is a multidimensional validated measure of gait capacity in people with iSCI [38]. It consists of seven items that are characteristics of daily life walking: walking and carrying a bag, the timed Up & Go test, walking on a carpeted area, avoiding obstacles, walking stairs, walking over a step, and walking through a door. Each task will be timed (s) and performed at comfortable walking speed using an assistive device (if needed) according to the protocol. The level of assistance needed will be assessed on a scale from 1 to 6 (scores ranging from “independent”, “one cane/crutch/rail”, “two canes/crutches/rails”, “walker”, “assistance from one person”, to “unable to complete the task”). The score for each item will be calculated by multiplying the time taken with the assistance needed. Each item is then normalized to the mean time of healthy individuals. Normalized scores for each item are summed. A low total score reflects better gait capacity. The SCI-FAP will be performed at T0 (baseline), T5, and T10 (after the intervention). The between-group difference in change of SCI-FAP score at T5 (after the intervention) versus T0 (baseline) will be analyzed.

##### The Dutch version of the system usability scale (D-SUS)

The D-SUS is a questionnaire comprising 10 items designed to evaluate the usability of a system [39]. Each item is scored on a 5-point Likert scale from “strongly disagree” to “strongly agree.” Item scores are converted to a total score ranging from 0 to 100, with a higher score indicating greater usability. A total score from 0 to 50 indicates “not acceptable”, from 51 to 67 indicates “marginal usability”, and from 68 to 100 indicates “acceptable usability.” The D-SUS will be delivered at T1 (after the Myosuit training sessions) and T5 (after the intervention) for the intervention group and at T6 (after the Myosuit training sessions) and T10 (after the intervention) for the control group. The D-SUS has been tested for its validity and reliability [39].

##### The Dutch version of the quebec user evaluation of satisfaction with assistive technology (D-QUEST)

The D-QUEST is a 12-item questionnaire that assesses user satisfaction with an assistive device (8 items), service provided (4 items), and overall satisfaction (average of 12 items) [40]. Each item is scored from 1 (“totally dissatisfied”) to 5 (“very satisfied”). A higher score indicates greater satisfaction. An item score of 4 and 5 will be considered as “satisfactory” [41]. In addition, the importance of each item is indicated by the frequency with which it has been indicated as one of the three most important items [41]. The D-QUEST will be delivered at T1 (after the Myosuit training sessions) and T5 (after the intervention) for the intervention group and at T6 (after the Myosuit training sessions) and T10 (after the intervention) for the control group. The D-QUEST has been tested for its validity and reliability [40].

##### Quality-adjusted life years (QALY) gain and costs

The European Quality of Life Five Dimension (EQ-5D-5L) will be used to calculate gained QALYs [42, 43]. The EQ-5D-5L is a questionnaire that measures a patient’s health state across five dimensions: mobility, self-care, usual activities, pain/discomfort, and anxiety/depression. Scores on each dimension range from 1 to 5, with a higher score indicating a better health state. The EQ-5D-5L will be delivered at T0 (baseline), T5, and T10 (after the intervention). Measurements at T0 (baseline) and T5 (after the intervention) will be analyzed. In addition, actual costs associated with the intervention (Myosuit program) will be calculated, including costs related to providing physical therapy, the Myosuit purchase costs, and the Myosuit maintenance costs. Costs associated with the conventional program are costs related to providing physical therapy. The costs for physical therapy will be calculated based on the average wages of current rehabilitation physiotherapy professionals in The Netherlands indicated by the Dutch Health Care Institute.

##### General and disease specific self-efficacy scale (GDSSeS)

The GDSSeS is a 10-item questionnaire designed to assess general self-confidence and confidence in self-managing one’s physical status. For this study, six items are added to assess self-confidence in walking. Each item is scored from 0 to 10, with higher scores indicating greater confidence. A total score is calculated by summing up the scores for all items. The GDSSeS will be delivered at T0 (baseline), T5, and T10 (after the intervention). Measurements at T0 (baseline) and T5 (after the intervention) will be analyzed.

#### Demographics

The following demographic data will be collected: sex, age (years), time since spinal cord injury (months), body mass index (BMI), spinal injury level according to the ASIA impairment scale [44], level of spinal cord injury, leg muscle strength assessed with the MRC scale [45], leg muscle tone assessed with the Ashworth Scale [46], and somatosensation of the lower limbs assessed with the ASIA impairment scale [44].

### Data management

The collected data will be entered in CastorEDC (www.castoredc.com), where each participant will receive a unique anonymous code. A number is assigned to the order of inclusion. The list with unique codes will be stored separately from the collected data. All authors will have access to the final dataset in CastorEDC until they are no longer involved in the study. All data will be stored for 15 years after the study has ended. An independent monitor is designated to the study and will conduct monitoring according to the Netherlands Federation of University Medical Centers (NFU) regulations [47] for “negligible risk intensity”, independent of investigators and sponsors. No other groups are involved in the trial oversight.

### Assessment of adherence and co-interventions

To enhance adherence to the study protocol, all training sessions and assessments are planned at baseline and participants have direct contact with the primary investigator (LV) about these dates during the study period. Adherence to the training protocol will be logged by the physical therapists. If participants will cancel a training session, an additional session will be scheduled. As for the 6-week home period, home use instructions will be given after the last training session, but participants will only have contact with the primary researcher regarding the assessments or in the case there is a technical problem with the Myosuit. Participants are asked to complete all assessments independent of how often the Myosuit is used at home. There are no restrictions with respect to usual care during the study period.

### Safety and adverse event reporting

The classification risk is estimated as “negligible risk” according to the NFU regulations [47]. According to protocol, adverse events will be logged and serious adverse events will be reported through the web portal ToetsingOnline to the accredited medical ethics committee.

### Sample size

An improvement of 500 steps per day is considered clinically relevant, corresponding to a 33% improvement of a baseline with 1500 steps per day [48]. Based on a stride time of 1.07 s, 500 steps per day corresponds to an increase of 4.5 min walking time per day [49]. For each group, a sample size of *N* = 14 is needed to demonstrate a difference in improvement of 500 steps per day between groups (SD = 400, *α* = 0.05, *β* = 0.10) [48]. Three patients will be added to each group (*N* = 17) allowing an 18% attrition rate; therefore, we aim to include a total of 34 participants. Sample size calculation is based on conducting analysis of variance (ANOVA) due to the absence of data for calculating a correlation that would be required for sample size calculation based on analysis of covariance (ANCOVA). Generally, statistical power of ANCOVA is higher than that of ANOVA.

### Statistical methods

For both the primary and secondary outcomes, an intention-to-treat analysis will be performed. For missing data, listwise deletion will be used. Additionally, the last observation carried forward method will be used in the sensitivity analysis.

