#### Primary outcome

To indicate group differences in walking time per day (average values of the first, third, and sixth week of the home period, e.g., T2–T4), an ANCOVA will be performed using the pre-intervention values (T0) as covariates.

A secondary analysis will be performed on walking time per day for the combined Myosuit home use periods (average values of the first, third, and sixth week of the home period (T2-T4) versus pre-intervention values (T0) for the intervention group and average values of the first, third, and sixth week of the home period (T7-T9) versus pre-intervention values (T4) for the control group) to investigate whether specific personal characteristics are related to improvement resulting from Myosuit use. This analysis involves a regression model with the difference in minutes walking time per day as dependent variable and personal characteristics (such as lesion level, ASIA score, and age) as independent variables. No other analyses are preplanned.

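### The primary analysis is labelled intention-to-treat, but listwise deletion makes it a complete-case analysis by allocated group, and last observation carried forward is its only check

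*Protocol article*

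**What the plan says.** Statistical methods, opening paragraph: "For both the primary and secondary outcomes, an intention-to-treat analysis will be performed". The next two sentences set the missing-data rules: "For missing data, listwise deletion will be used. Additionally, the last observation carried forward method will be used in the sensitivity analysis". The Primary outcome paragraph of the same section specifies an ANCOVA of the T2–T4 mean with T0 as covariate, adds a regression on personal characteristics, and closes with "No other analyses are preplanned".

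Four other places bear on the point:

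- **Sample size:** 14 per group are needed, raised to 17, "allowing an 18% attrition rate".
- **Assessments, Primary outcome:** the activity-monitor data from the three home-period weeks "will be averaged across all days".
- **Procedure:** after the Myosuit training sessions, "participants will perform a test to receive a certificate for using the Myosuit themselves at home". In the randomised comparison only the Myosuit arm meets this step before T2.
- **Assessment of adherence and co-interventions:** all assessments are requested however much or little the suit is used at home.

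**The concern.** An intention-to-treat estimate concerns everyone randomised. Listwise deletion restricts the analysis to people with complete data, so the label and the rule describe different analyses. The article fixes both, so this is not a detail left to an analysis plan that is not shown.

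Three features make the gap matter here.

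- **Loss is expected.** The trial is small and the sample size budgets for it.
- **Loss may not be neutral.** Participants know their arm, and control participants receive the Myosuit only after finishing the conventional programme, which gives them a reason to stay that the Myosuit arm lacks. Dropout could therefore differ by arm and relate to outcome.
- **The rule is incomplete for this outcome.** The outcome is one mean built from three weekly recordings. The text does not say whether a missing week removes the participant or whether the remaining days are averaged. The first discards valid data. The second changes the weight of each week. The Blinding section justifies unblinded analysis by saying the analyses are defined in advance, so this should not be settled after the data are seen.

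The only robustness check, LOCF, treats carried values as if they had been observed and assumes nothing changes after the last recording.

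**Working it through.** **Inputs from the Sample size section:** difference 500 steps/day, SD 400, α = 0.05 (two-sided assumed, as sidedness is not stated), β = 0.10, stride time 1.07 s, 14 per group raised to 17.

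**1. The plan's own figure.** n = 2 × [400 × (1.960 + 1.282) / 500]² = 13.45, rounded up to 14 per group. This reproduces. Power from the t distribution at 14 per group is 88.9%. Attrition is 3/17 = 17.6%, stated as 18%, and 14 / (1 − 3/17) = 17. Thus 14 is the number expected to remain after loss: the trial is sized for completers.

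**2. How many may be left out.** 2 × 3 = 6 of 34 (17.6%).

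**3. Effect on the estimate, assumed scenario.** Suppose completers in the Myosuit arm gain 500 steps/day over control and k of its 17 members are lost with a true gain of c. The all-randomised effect is [(17 − k) × 500 + k × c] / 17, whereas listwise deletion reports 500.

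| k lost | c | All-randomised effect | Overstatement |
|---|---|---|---|
| 1 | 0 | 471 | 6% |
| 2 | 0 | 441 | 13% |
| 3 | 0 | 412 | 21% |
| 3 | +250 | 456 | 10% |
| 3 | −250 | 368 | 36% |

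For k = 3, c = 0: (14 × 500) / 17 = 412, and 500 / 412 = 1.21. In minutes, 500 × 1.07 / 120 = 4.46 and 412 × 1.07 / 120 = 3.67.

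**4. Effect on type I error, assumed scenario.** A simulation of 40,000 trials had 17 per arm, SD 400, no true effect and a t-test on change. Three Myosuit participants were lost according to a score correlated with poor change, and there was no loss in the control arm.

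| Correlation of dropout with poor change | Listwise bias (steps/day) | Type I error, listwise | Type I error, LOCF from T0 |
|---|---|---|---|
| 0 | about 0 | 5.0% | 5.0% |
| 0.3 | 36 | 5.8% | 5.7% |
| 0.5 | 59 | 7.4% | 7.0% |
| 0.7 | 84 | 9.3% | 8.7% |
| 1.0 | 118 | 15.3% | 13.7% |

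With unrelated loss nothing is biased. With selective loss in one arm, LOCF carries most of the same error and so would not reliably reveal it.

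The documents give no dropout mechanism. Steps 3 and 4 show a range under stated assumptions and do not predict what will happen.

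**The case against.** The strongest reply is that complete-case ANCOVA with one post-treatment mean is valid if missingness depends only on arm and baseline, and that the plan already limits loss: assessments are requested regardless of suit use, cancelled sessions are rescheduled, and the monitor is worn on the thigh and needs no suit. This stands as a reason not to presume bias. It does not reconcile the label with the rule, and validity then rests on an assumption that the plan gives no adequate means of testing.

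Four stronger readings are tempting, and the documents do not support them.

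- **That the certification test creates a loss path in the Myosuit arm.** This is inference. Nothing says that failing the test ends follow-up or measurement, and the adherence section points the other way for non-use. It is silent on non-certification, which is a reason to state the rule.
- **That the bias favours the suit, for instance through a novelty effect in week 1.** No such effect is described. Use could equally grow with familiarity, in which case early values carried forward would understate the effect. Selective loss of poor performers from the control arm would bias against the suit.
- **That LOCF always hides the problem.** If the three lost participants truly gained nothing and left before T2, carrying T0 forward gives zero change and returns 412 steps/day. LOCF is right in that case and wrong in others, so it is unreliable but not uniformly inflating.
- **That unusable recordings cut power to about 80%.** Suppose each of the four recordings has a 5% chance of being unusable (a rate not in the documents). Then 1 − 0.95⁴ = 18.5% of participants lack at least one. Taking that from 14 per arm leaves about 11 and power of 79.6%, but the 14 already allow for attrition. Applied to those enrolled, 17 × 0.95⁴ = 13.8, about 14 per arm, with power of about 89%.

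It is also fair to say that a mixed model alone does not bring back anyone with no T2–T4 data. The fix has to cover them separately.

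**Conclusion.** The point holds as a mismatch between label and rule with a weak sensitivity analysis. It does not demonstrate bias. What is certain from the text is that the intention-to-treat label sits beside a complete-case rule, LOCF is the only check, and the planned attrition allows up to 6 of 34 randomised participants to be missing from the primary result. Valid T2 or T3 data are also lost if deletion is applied to single weeks, which the text leaves open.

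What is conditional is any distortion of the effect. It requires dropout related to outcome and, for the scenarios above, concentrated in the Myosuit arm. Under the central assumed scenario the effect is reported as 500 instead of 412 steps/day (+21%). If loss is unrelated to outcome the bias is nil. The direction is unknown. This should be fixed, but it does not by itself invalidate the design or the sample size.

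**What to change.** 1. **Primary model.** Analyse the weekly means at T2, T3 and T4 in a repeated-measures mixed model with arm × week, T0 value and walking-speed stratum, using Kenward-Roger degrees of freedom. Make the equally weighted average over the three weeks the primary contrast, and keep every randomised participant with any T2–T4 data.
2. **Follow-up.** State that T2–T4 activity-monitor recordings are collected and analysed as randomised whatever the result of the certification test, in line with the adherence section.
3. **Sensitivity analysis.** Replace LOCF with delta-adjusted or control-based multiple imputation that includes participants with no post-baseline data, since the mixed model cannot.
4. **If the primary rule is kept,** call it a complete-case analysis by allocated group, and say what happens when one week is missing.

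The cost is wording, slightly more analysis work and a covariance choice in a small sample. The sample size is unaffected. The Trial status section reports 23 of 34 participants included, so the change can be made by amendment provided that it precedes the analysis.
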